### Intervention

#### Brief intervention course (BIC)

The participating GPs will receive a one day course held by headache specialists (CL and [name]). It includes general lectures about migraine, tension-type headache and chronic headaches, especially MOH. A presentation of the Brief Information scheme will be given with practical instructions examplified by role play. Participating GPs will earn CME credits by the Norwegian Medical Association as part of the GP training curriculum. In general, most of these physicians have previously not received specific training in the handling of MOH. However, information on possible previous participation in such training will be collected.

#### Brief intervention (BI)

GPs allocated to the BIC will receive information about screening-positive patients on their lists. These patients will be invited to a consultation for headache by the GP. BI will then be performed as follows (for more details see flow-chart, Figure 
2):

**Figure 2 F2:**
[figure not shown]
Flow-chart of GPs Brief Intervention for MOH strategy.

1. Use of the SDS questionnaire (Table 
1) to identify patients at risk for MOH, i.e. SDS cut-off values ≥5 (females) and ≥4 (males) 
[30,35,36]. Inform the patient that he or she is identified as being at risk for MOH. Patients with SDS score under cut-off will also receive a structured intervention and information about the relationship between drug intake and headache and the importance of staying within “safe levels” of medication use.

2. Give short structured information about MOH and the association between medication overuse and chronic headache.

3. Give specific individualised information and advice regarding reduction of acute headache medication.

**Table 1 T1:** The five questions of the Severity Dependence Scale (SDS) adapted for headache medication

1.	Do you think your use of headache medication was out of control? (never/almost never=0, sometimes=1, often=2, always/nearly always=3)
2.	Did the prospect of missing a dose make you anxious or worried? (scoring as for question 1)
3.	Did you worry about your use of your headache medication? (scoring as for question 1)
4.	Did you wish you could stop? (scoring as for question 1)
5.	How difficult would you find it to stop or go without your headache medication? (not difficult=0, quite difficult=1, very difficult=2, impossible=3)

#### Headache classification

The headaches will be classified according to explicit diagnostic criteria of the ICHD-II and it‘s relevant revisions 
[83-86]. In this study we have defined chronic headache as 15 or more headache days per month for at least 3 months and/or 180 or more headache days per year as the ICHD-II does not provide an explicit definition for all headache diagnoses. The ICHD-II diagnosis will be made by the first author and by consensus in the project team based on the 3 month follow-up interview.

#### Headache diary

A modified version of a validated headache diary 
[87,88] will be used in order to prospectively record data on headache frequency, headache intensity (VAS) and medication. We have also added self-reported number of sick-leave days. The completion of the diary for a two week period will be required at baseline, at three, six and twelve months for both BI and BAU patients. Written instructions for the completion of the diary will be mailed to the patients.

#### Blinded three months follow-up

Three months after the intervention (or after recruitment to the BAU arm), the patients will be invited to a clinical interview with an examination focusing on diagnosis of headache, relevant comorbidity, use and quantification of prescription drugs as well as OTC drugs. The interviewer will be blinded as to which study arm the patients are allocated to and the patients will be blinded as to intervention, outcomes and aim of study.

Additional questionnaires will be completed by the patients (Table 
2) in order to cover headache related health and quality of life, use of health services, socioeconomic and demographic data.

**Table 2 T2:** Validated questionnaires used for additional outcomes with comments regarding relevance for present study and references to the literature list

***Validated questionnaire***	***Description of questionnaire***	***Importance in present study***	***Ref.***
**Short Form-36 (SF-36)**	Most used general QoL questionnaire	Enables quality of life comparison with non-headache patients from the general population ., normal material for Norwegian population exists	[89-91]
**Migraine Disability Assessment (MIDAS) Headache Impact Test – 6 (HIT-6)**	Most used headache specific QoL instruments, recommended for RCTs of headache treatment	Enables comparison between various headache categories	[92,93]
**Severity of Dependence Scale (SDS)**	Validated for detection of MOH in previous studies	Simple identification of MOH patients, comparison against scores for other addictive drugs	[58,94]
**Mini International Neuropsychiatric Interview (MINI)**	Validated structured interview for DSM-IV based diagnosis of substance dependency	Gold standard for dependency for validation of SDS	[58,94]
**Eysenck Personality Questionnaire (EPQ)**	Widely used personality scale both in relation to drug dependency and in more general	Assessment of personality as a factor which may affect outcomes after a behavioural intervention, Norwegian population standards exist	[95-97]
**Hopkins Symptom Checklist-25 (HSCL-25)**	Well validated scale for symptoms of psychological distress	Supplement to Eysenck for assessing degree of distress which may affect outcomes of behavioural intervention, Norwegian population standards exist	[98-100]
**Hospitality and Anxiety Depression Scale (HADs)**	Most used scale in clinical materials for scoring depressive and anxiety symptoms	Assessment of depression and anxiety as comorbidities of chronic headache which may affect outcomes of intervention, Norwegian population standards exist	[101,102]

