**Methods/Design:**

A double-blinded cluster randomised parallel controlled trial (RCT) of BI vs. business as usual. Intervention will be performed in primary care by GPs trained in BI. Patients with MOH will be identified through a simple screening questionnaire sent to patients on the GPs lists. The BI method involves an approach for identifying patients with high likelihood of MOH using simple questions about headache frequency and the SDS score. Feedback is given to the individual patient on his/her score and consequences this might have regarding the individual risk of medication overuse contributing to their headache. Finally, advice is given regarding measures to be taken, how the patient should proceed and the possible gains for the patient. The participating patients complete a headache diary and receive a clinical interview and neurological examination by a GP experienced in headache diagnostics three months after the intervention. Primary outcomes are number of headache days and number of medication days per month at 3 months. Secondary outcomes include proportions with 25 and 50% improvement at 3 months and maintenance of improvement and quality of life after 12 months.

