## Methods/Design

Our hypothesis is that BI is more effective than BAU. The hypothesis will be tested using a double-blinded cluster randomised parallel controlled clinical trial in primary care comparing BI and BAU three months after study inclusion and with additional open one year follow-up (Figure 
1).

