#### Patients

A short validated screening questionnaire for headache 
[80,81] including questions about headache frequency, intensity (as recorded on a visual analogue scale (VAS) 
[82]), presence of migraine and medication use will be mailed to all 18–50 year old patients on participating GPs’ patient lists. Names and addresses will be extracted from GP lists using a specially designed software (Mediata Ltd, Tønsberg, Norway). One written reminder will be sent to non-responding patients.

All patients with 15 or more days with self-reported headache per month and headache medication utilization on 10 days or more per month will be invited to participate.

Patients unable to participate in an interview in Norwegian will be excluded.

Baseline patient information (screening questionnaire and headache diary) will be collected by the Akershus University hospital research administration unit before any study-related contact between patient and their GP.

To avoid unblinding and carry-over of information from the BI to BAU, both GPs and patients will initially only receive basic information that this study aims to evaluate headache and headache care in primary care.

After the intervention part, all follow-ups will be conducted by the first author ([name]), who will be blinded in relation to which treatment the participant has received. All participating patients will receive a semi-structured interview and clinical and neurological examination.

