### Outcome measures

Outcome measures are listed in Table 
3. Primary outcomes are headache days and medication days per month comparing the two arms and change compared to baseline. With a simple, non-medication intervention as the present, any significant improvement in these parameters is judged to be of relevance. Proportions fulfilling commonly used clinical definitions of chronic headache (≥15 days/month) and medication overuse 
[75-78] at follow up are also clinically relevant and included as secondary outcomes. In addition, since clinically relevant outcomes in medication studies have been suggested to be 25 to 50% improvement in headache days and headache index, these are also included as secondary outcomes. 

**Table 3 T3:** Outcome measures and time points for application of the various outcomes (statistical calculations are further described in the Statistics section)

	**3 months**	**12 months**

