#### Statistics

All analyses will be focused at the patient level (inference unit will be patient). We will perform a series of frequency analyses tabulating outcome variables against various explanatory variables and/or confounders. Suitable descriptive statistics will be used. Since individual observations within the same cluster (ie. patients of one GP) may be correlated, the intra-cluster (intra-class) correlation coefficient (ICC) measuring such a “clustering effect” and estimating the relative variability within and between clusters will be calculated for both intervention- and control groups. Analysis of differences between BI- and BAU groups based on mixed linear models (MLM) will be performed to account for the hierarchical nature of data, where the main point is to allow variation to be modelled at each level of the data, for example, the GP and the patient level. 95% confidence intervals will be used.

Analysis based on prespecified hypotheses regarding the two primary and the secondary outcomes will be performed as hypothesis testing on the entire dataset and Bonferroni corrections will be used for multiple comparisons. For evaluation of possible outcome predictors where no prior data from this population exist, split file analysis 
[103] will be used. The splitting of the data set will be performed prior to any analyses of primary and/or secondary outcomes.

The intention-to-treat principle will be followed by including all patients with at least one follow-up response. Missing values will be handled using multiple imputation techniques.

SPSS 16.0 and SAS will be used for statistical analyses.

Registration of electronic data from the semi-structured interviews will be done by using Snap Survey (Snap Survey, London, UK).

The participating patients will receive a weekly reminder regarding the headache diary via mobile phone (SMS) during each two weeks diary period at three, six and twelve months, respectively.

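### The three-month clock for the primary assessment starts at the intervention in BI but at recruitment in BAU, which contradicts the common starting point in Methods/Design and leaves BI non-attenders without a due date

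*Protocol article*

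**What the plan says.** Three sections of the protocol article fix the time of the main comparison, and they differ.

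- **Methods/Design** gives one starting point for both arms: "comparing BI and BAU three months after study inclusion".
- **Blinded three months follow-up** gives one per arm: "Three months after the intervention (or after recruitment to the BAU arm), the patients will be invited to a clinical interview".
- **The Abstract** (Methods/Design paragraph) places the interview and examination "three months after the intervention" for participating patients in general, without saying what this means in BAU.

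The Headache diary section says that diaries "will be required at baseline, at three, six and twelve months for both BI and BAU patients", without defining day 0.

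Four further statements bear on the point.

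- Patients: the screening questionnaire and baseline diary are collected "before any study-related contact between patient and their GP". The same section plans an interview and examination for everyone taking part.
- Brief intervention (BI): the GP is told which listed patients screened positive, and then "These patients will be invited to a consultation for headache by the GP".
- Outcome measures: "Primary outcomes are headache days and medication days per month comparing the two arms and change compared to baseline".
- Statistics: intention to treat is to be followed by "including all patients with at least one follow-up response".

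**The concern.** In a parallel comparison both arms should be measured at the same time from a starting point that does not depend on the treatment received. The follow-up section sets the BI date by an event after allocation that BAU patients do not have. The steps between recruitment and that event (list to the GP, invitation, appointment) take time in BI only.

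Patients enter because their self-reported counts are high: 15 or more headache days and 10 or more medication days per month. The Discussion itself expects some improvement in controls and lists regression to the mean and measurement effects among the possible reasons. If such change is still going on at three months, an arm measured later shows more of it, and the excess is counted as an effect of BI. Randomisation does not remove this, because the difference arises after allocation. A larger sample does not remove it either.

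Two features raise the stakes. Outcome measures sets no minimum relevant effect and treats any significant improvement as relevant. Ethics and data security lets a significant three-month benefit lead to training of the BAU GPs.

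Separately, a BI patient who does not take up the invitation has no intervention date, so the rule gives no date for the visit. In BAU every patient has one.

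**Working it through.** No stated figure is in dispute, so the check is mainly textual, with arithmetic on assumed lags to show scale.

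**Step 1. Order of events in BI.** Baseline comes before study contact with the GP (Patients). The invitation and consultation come after it (Brief intervention). The intervention therefore cannot precede baseline, and it coincides with recruitment only if the lag is zero.

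**Step 2. Time from recruitment to assessment under the follow-up section's rule.** Let L be the lag from recruitment to consultation, in weeks, and take three months as 13 weeks.

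- BAU: 13
- BI: 13 + L
- Ratio: (13 + L) / 13

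L is not in the article. The range 0 to 12 weeks is an assumption.

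| Assumed L (weeks) | BI (weeks) | BAU (weeks) | BI longer by |
|---|---|---|---|
| 0 | 13 | 13 | 0% |
| 2 | 15 | 13 | 15% |
| 4 | 17 | 13 | 31% |
| 8 | 21 | 13 | 62% |
| 12 | 25 | 13 | 92% |

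Screening and recruitment are described as the same process in both arms. Assuming the interval from baseline to recruitment is also the same, the difference in time since baseline is again L.

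**Step 3. BI patients without a due date.** The planned total is 160 patients, with half of the CME groups in each arm. Assuming equal numbers of patients, that is 160 / 2 = 80 in BI. The share not attending is not given. For assumed shares of 5%, 10%, 20% and 30%, the numbers are 80 × 0.05 = 4, 80 × 0.10 = 8, 80 × 0.20 = 16 and 80 × 0.30 = 24.

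**Step 4. The same quantities with a common anchor at inclusion.** Taking inclusion to coincide with recruitment, both arms are assessed at about 13 weeks, the difference is 0 for any L, and every patient has a date. The price is that time since the consultation in BI becomes 13 − L: 13, 11, 9, 5 or 1 weeks for L = 0, 2, 4, 8 or 12.

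**The case against.** **Timing from the intervention has a rationale.** It gives every treated patient the same time after the consultation. That is fair, and Step 4 shows what is lost otherwise. It does not justify leaving BAU on a different clock, because BAU can be given a matching index date.

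**The misalignment is read from the text and not observed.** Recruitment to the BAU arm is not defined, and the study flow chart (Figure 1) is not available here. Its caption mentions the timing of the intervention for BI and BAU respectively, so the figure may place a comparable date in BAU. This limits certainty about how visits would actually be scheduled. It does not remove the conflict between the two written rules.

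**A reader might infer a definite bias in favour of BI.** For example, an assumed lag of 1 to 2 months and an assumed untreated fall of 0.5 to 1 day per month for each month elapsed would give 0.5 × 1 = 0.5 to 1 × 2 = 2 days per month. The article supports neither input. Both ranges exclude zero by choice; started at zero, they give 0 to 2 days. Nor does regression to the mean imply a steady fall: it appears on re-measurement and may be complete by three months, so a later visit may add almost none. The Discussion mentions it as one possible reason for small reductions in control groups of alcohol studies, and the condition studied here is by definition persistent.

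**A reader might also infer that BI non-attenders are excluded from the outcome.** The article does not say so. The Patients section plans an interview for all participants, and the intention-to-treat statement does not require that BI was delivered. What is missing is a due date under the follow-up section's rule. The full protocol, not shown, may hold a fallback.

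**Conclusion.** The point holds as a contradiction within the article about the time zero of the primary comparison. Methods/Design gives both arms a common start; the follow-up section does not. Under the follow-up section's rule, the interval from baseline to assessment is longer in BI by the unstated lag, and equal only if that lag is zero. The same rule gives BI non-attenders no due date, although the plan intends to follow and analyse them.

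The article gives no basis for a bias in days. The difference in timing is 0 to 12 weeks under the assumed lags. Its effect on headache and medication days depends on change unrelated to BI that is still under way at three months, and may be close to zero. If such change is continued improvement, it would favour BI. The point deserves correction because it defines when both primary outcomes are measured and is cheap to settle before follow-up is scheduled. No bias has been demonstrated.

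**What to change.** Choose one time zero, apply it to every patient whether or not the consultation took place, and make the Abstract, Methods/Design, Headache diary and Blinded three months follow-up sections agree on it. Either of two rules would do.

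1. **Inclusion or baseline in both arms**, as Methods/Design already says. This is the simplest rule and dates every patient. The cost is that time since the consultation varies among BI patients and falls short of three months by the lag. The shortfall is small if consultations follow quickly and substantial if they do not (Step 4).
2. **A BAU index date matched to the BI lag from recruitment to consultation**, with the same index rule for BI patients who do not attend. This keeps about three months after the consultation for those treated. The cost is more scheduling work, and a median lag aligns the arms only on average.

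Under either rule, define day 0 of the diary schedule in the same terms. Recording the consultation date, and reporting the interval from baseline to assessment by arm, would show how large any remaining difference is. The change needs wording and a scheduling rule for the research office, with no extra patients or visits.

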[80,81]. However, especially among those with chronic or co-occurring headache types, diagnosing headaches is not always easy. The gold standard for making a specific headache diagnosis is an interview combined with a physical and neurological examination by a physician experienced in headache diagnostics. All patients will be diagnosed based on interviews by a GP trained and experienced in headache diagnostics also in order to avoid inter-observer variation ([name]).

Some of our data will be based on retrospective self-reports and therefore open to recall bias, although here is no reason to suspect systematic bias. In order to counteract this, we will also use headache data from prospective headache diaries 
[87]. Recent studies using a similar headache diary with written instructions before first consultation found high usefulness, acceptability and comprehensibility of the diary as well as good compliance and completeness of data 
[105,106]. We will use the headache diary for periods of two weeks. This period may seem too short for infrequent forms of headache, but in our sample of chronic sufferers this should not be a problem. In addition, a longer headache registration period may reduce compliance and cause greater interference with the cohort.

A common finding in many brief intervention studies and RCTs on alcohol use, are small reductions in alcohol consumption at follow-up also in the control group 
[73,107]. Possible reasons for this may be motivational effects of screening, sensitization to screening/measurements/follow-up, non-intended advice also in BAU group, and “regression towards the mean”. In this study we have tried to minimize most assessment effects by doing a double-blinded parallel RCT, and the screening questionnaire about medication use for headache is embedded with other questions about headache in the very short screening questionnaire. The control group will not receive the SDS screening before the three months follow-up and will therefore not be affected by this.

The SDS has not been validated against other measurements of dependency in MOH sufferers and, indeed, there is still much discussion as to whether MOH represents dependency 
[50-55,57]. Being fully aware of this, we will use the SDS score, not as an attempt to define dependency, but rather to distinguish between chronic headache subjects with and without medication overuse 
[30,35].

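### The trial is called double-blinded, but BI patients and their GPs know the intervention; only the interviewer is masked to arm, and both primary outcomes are patient-reported

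*Protocol article*

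**What the plan says.** The double-blind label appears in the Abstract, at the end of the Background, in Methods/Design and in the Discussion. Methods/Design states: "The hypothesis will be tested using a double-blinded cluster randomised parallel controlled clinical trial in primary care comparing BI and BAU". It sets this 3-month comparison against a one-year follow-up that it calls open.

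The section Blinded three months follow-up makes two claims. For the assessor: "The interviewer will be blinded as to which study arm the patients are allocated to". For the participants: "the patients will be blinded as to intervention, outcomes and aim of study".

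The device that supports masking of patients and GPs is in the Patients subsection of the recruitment section: "both GPs and patients will initially only receive basic information that this study aims to evaluate headache and headache care in primary care".

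The section Brief intervention (BI) says of screening-positive patients: "These patients will be invited to a consultation for headache by the GP". The numbered steps under Figure 2 then list the SDS, structured information on overuse and chronic headache, and individual advice on reducing acute medication. For those at or above the SDS cut-off, the step reads: "Inform the patient that he or she is identified as being at risk for MOH". Patients below the cut-off also receive a structured intervention about drug intake and headache.

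The Discussion gives the design credit for limiting assessment effects: "we have tried to minimize most assessment effects by doing a double-blinded parallel RCT". On retrospective self-reports, it accepts that recall may be faulty but sees no grounds for expecting the error to be systematic.

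**The concern.** A patient who has been scored on a dependence scale, taught about medication overuse and advised to take less is not blind to the intervention. The advice concerns acute medication, and medication days is one of the two primary outcomes, so the patient has also been told what is meant to change. The usual-care (BAU) arm receives none of this from the study.

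Headache days and medication days are both reported by the patient. Masking the interviewer guards against bias in how the questions are put and recorded. It does not guard against an advised patient reporting fewer days because fewer is what was asked for. If the label stands, the trial report will claim a protection that the design does not give to its primary outcomes. The Outcome measures section adds to the stakes: it counts any significant improvement as relevant, so no minimum effect size stands between a small reporting shift and a positive conclusion.

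**Working it through.** The protocol gives no figure on this point. The check is a comparison of sections, followed by one illustration.

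**Who knows what at 3 months**

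| Party | What the protocol provides | Consequence |
|---|---|---|
| BI GPs | One-day course, then deliver BI to their own patients | Not blind to the intervention |
| BI patients, SDS at or above cut-off | SDS, at-risk message, information, advice on reduction | Not blind to the intervention or to the target of one primary outcome |
| BI patients, SDS below cut-off | SDS, structured intervention on drug intake and headache | Not blind to the intervention; no at-risk message |
| BAU patients | No SDS before 3 months, usual practice | Masking of aim better preserved |
| Interviewer | Masked to arm | Blind as planned |

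The basic-information device applies at the start. It may leave patients and GPs unaware of the hypothesis and of the other arm. It does not describe what BI patients know after the consultation, which is when the primary outcomes are measured.

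**How the primary outcomes are measured.** Table 3 lists the two outcomes as primary at 3 months and lists the diary versions separately as secondary. This suggests that the primary versions come from the interview. Either way, the patient is the source. The two-week diary is prospective and so reduces recall error, but the patient completes it.

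**Illustration of sensitivity (assumed inputs).** Suppose BI has no true effect and BI patients under-report by *b* standard deviations. Both *b* and the ICC of 0.1 are assumptions. An ICC of 0.5 is the protocol's own worst case. From Power calculations: 160 patients, 20 GPs, 8 per GP, hence 80 per arm.

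- Design effect = 1 + (8 − 1) × ICC: 1 at ICC 0, 1.7 at ICC 0.1, 4.5 at ICC 0.5.
- Effective n per arm = 80 / design effect: 80, 47.1, 17.8.
- Shift of the test statistic = *b* × √(effective n / 2).
- Rejection rate = P(|Z + shift| > 1.96) for a two-sided 5% test.

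| *b* (SD) | ICC 0 | ICC 0.1 | ICC 0.5 |
|---|---|---|---|
| 0.1 | 10% | 8% | 6% |
| 0.2 | 24% | 16% | 9% |
| 0.3 | 48% | 31% | 15% |

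At *b* = 0.25 (for example 2 days with an assumed SD of 8 days), the shift is 0.25 × √(47.1/2) = 1.21 at ICC 0.1, giving 22.8%. At ICC 0.5 it is 0.25 × √(17.8/2) = 0.75, giving 11.6%.

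The protocol plans Bonferroni corrections. If that means 2.5% for each of two primary tests, the rates for *b* = 0.2 become 16.5%, 10.2% and 5.2% at ICC 0, 0.1 and 0.5.

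The table shows how the test would respond to a shift. It is no evidence that a shift occurs.

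**The case against.** **Masking is partial, not absent.** A reader might infer that patients are masked to nothing and that the trial is simply open. The documents do not support that. Disclosure is limited at the start, baseline data are collected before any study-related GP contact, and BI takes place with the patient's own GP. Patients may know the advice they received and still not know that a comparison exists. This stands, and the corrected label should say so.

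**The Discussion sentence is partly valid.** A reader might take "we have tried to minimize most assessment effects by doing a double-blinded parallel RCT" as a claim that blinding removes desirability bias in BI patients. Its paragraph is about improvement in control groups: reactions to screening and measurement, unintended advice and regression to the mean. Withholding the aim can plausibly reduce such reactivity. The sentence needs narrowing, not deletion.

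**Not every BI patient is told of being at risk.** That message depends on the SDS cut-off. This stands, but those below the cut-off are still exposed to the content of the intervention.

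**Failure of the interviewer's masking is not shown.** A reader might infer it because the follow-up also covers health-service use and the SDS. The additional questionnaires are described as patient-completed, the document does not say the interviewer sees them first, and the SDS is collected in both arms, so a score does not itself reveal a BI consultation. Leakage is a risk only.

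**A behavioural intervention can hardly be hidden from its recipients.** This is true. The criticism is of the claim, not of the choice of design. Nor is it a detail that an article may leave to a fuller document: patient blinding is stated outright, and the article's own account of BI contradicts it.

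**Conclusion.** The point holds as a stated property that the design does not have. At the primary endpoint, BI GPs and the patients who receive BI are not blind to the intervention, and those patients know the target of the medication-days outcome. What the design does have is an interviewer masked to arm, and limited disclosure of the hypothesis and the other arm to patients and GPs.

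Both primary outcomes are affected, because both rest on patient report and the diaries share that source. Differential reporting is possible. Neither its presence nor its size can be derived from the document. A reader might take the rejection rates of roughly 6% to 48% as an estimate of the trial's false-positive risk. They are not: they follow from assumed shifts and ICCs and show sensitivity only.

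The correction should be made because the label is repeated throughout and because the Discussion draws on it when it weighs possible bias. It changes no treatment, sample size, endpoint or analysis.

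**What to change.** 1. **Label.** Describe the trial throughout as outcome-assessor-blinded, with limited disclosure of the aim and the comparison to patients and GPs. In Blinded three months follow-up, replace the statement that patients are blinded to intervention, outcomes and aim with what they are and are not told.
2. **Discussion.** Reword the sentence on assessment effects so that blinding is credited only with reducing interviewer bias and control-arm reactivity. Replace the statement that systematic bias in self-reports need not be suspected with an acknowledgement that BI patients may report differently, to be kept in view when the primary outcomes are interpreted.
3. **Three-month visit.** As a safeguard for the interviewer's masking, record headache days and medication days before the SDS, the MINI and the health-service items, and ask patients not to mention recent GP contacts until then.

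The first two changes make the claim accurate, and the third protects the masking that exists. None of them removes reporting bias in advised patients, which is why the acknowledgement is needed. The cost is a less favourable design label and a fixed question order.
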